### **Versie voor deelnemende bewoners**

*(in te vullen door de onderzoeker; bevragen bij de (hoofd)verpleegkundige of de vertegenwoordiger van de bewoner):*

1. Gelieve het uniek studie nummer van de deelnemer in te vullen.
2. Neemt de bewoner nog deel aan de studie (zal deze vragenlijst vervolledigd worden)?  
ja/neen  
Zo neen, waarom niet?
  - a. Vermoedelijk of bewezen COVID-overlijden (datum overlijden)
  - b. Niet-COVID-19 gerelateerd overlijden (datum overlijden)
  - c. Bewoner wenst niet meer deel te nemen

*Vraag 3 wordt enkel toegevoegd indien voordien neen werd geantwoord.*

3. Is bewoner gevaccineerd tegen COVID-19?
  - a. Ja, 1 dosis
  - b. Ja, 2 dosissen
  - c. Neen
  - d. Zo ja, welk vaccin werd toegediend
    - i. Het AstraZeneca/Oxford vaccin
    - ii. Het BioNtech-Pfizer vaccin
    - iii. Het Moderna vaccin
    - iv. andere
  - e. Zo ja, datum van vaccinatie (eerste spuit).
- 4.

5. Is de deelnemer in de afgelopen twee maanden getest geweest op het coronavirus (via PCR/ag-sneltest/of radiologisch via CT-scan)? Ja/Nee
6. Zo, ja. Is de deelnemer in de afgelopen 2 maand (tussen de vorige testronde en nu) **positief** getest op het coronavirus?
  - Ja, via PCR-test (test waarbij men via een neuswisser een staal afneemt en u na labo-analyse het resultaat krijgt)
  - Ja, via antigen sneltest (test waarbij men via neuswisser een staal afneemt en men binnen het kwartier het resultaat kan aflezen)
  - Ja, radiologisch, via een CT-scan
  - Neen
7. Zo ja, datum van 1ste positieve PCR-test of sneltest de voorbije 2 maanden (bij benadering)?
8. Indien de COVID-19 radiologisch bevestigd werd via een CT-scan, vermeld de datum waarop dit is gebeurd.
9. Heeft de deelnemer in de afgelopen 2 maand (tussen de vorige testronde en nu) een periode 1 of meerdere van volgende symptomen ervaren, zonder dat hier een duidelijke verklaring voor was? Duid aan wat van toepassing is (meerdere antwoordmogelijkheden).
  - Hoest
  - Kortademigheid
  - Pijn op de borst
  - Smaakverlies
  - Geurverlies
  - Verergering van chronische respiratoire aandoeningen (vb. COPD, astma, chronische hoest,...)
  - Koorts
  - Spierpijn
  - Vermoeidheid
  - Loopneus/verstopte neus
  - Keelpijn
  - Hoofdpijn
  - Verlies van eetlust
  - Diarree
  - Acute verwardheid
  - Plotse val
10. Zo ja, wanneer heeft de deelnemer, bij benadering, deze symptomen ervaren? Gelieve de dag aan te geven waarop deze symptomen zijn begonnen.
11. Indien van toepassing, is de deelnemer gevaccineerd met een vaccin tegen COVID-19?  
Zo ja, datum van de vaccinatie (*Deze vraag zal ingevoerd worden zodra van toepassing*)

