## **2.5 Sample size**

To assess the cumulative incidence after 10 months of follow-up in residential care centers in Belgium a sample of 381 participants (residents & staff) is required to estimate a proportion of 0.5 with a half-width of 5%, using a 95% Wilson score CI. As residents/staff are clustered within care facilities, the sample size will be augmented by the design effect. Assuming, 15 participants (7 residents and 8 staff) per institution after 10 months of follow-up, and an ICC of 0.12, the design effect is  $2.68 = (1 + 0.12 \times (15 - 1))$ . The total sample size required is  $1022 = 381 \times 2.68$ . At least 69 institutions, each including 15 participants, need to be included in this study, which brings the total sample size to 1035 after 10 months follow-up. In order to obtain at least 15 participants, in 69 institutions after 10 months of follow-up, assuming a drop-out rate of 0.2 and 0.4 for staff (changes in staff, sick leave and holidays) and residents (deceased, hospitalized or transferred residents), would require 22 sero-negative participants per care facility, (10 staff, 12 residents) in all 69 institutions. Assuming a seroprevalence rate of 0.5 at the baseline moment of the study would require 44 participants per care facility, (20 staff, 24 residents) in all 69 institutions.

A final sample size calculation will be performed to check whether the sample size obtained for the second research question will be sufficient for the analysis of the first research question.

To assess the seroprevalence in residential care centers in Belgium a sample of 381 participants (residents & staff) is required to estimate a seroprevalence of 0.5 with a half-width of 5%, using a 95% Wilson score CI.

As residents/staff are clustered within care facilities, the sample size will be augmented by the design effect. Based on the previous calculation, 44 participants (24 residents and 20 staff) will be sampled per institution. Assuming an ICC of 0.12, the design effect is  $6.16 = (1 + 0.12 \times (44 - 1))$ . The total sample size required is  $2347 = 381 \times 6.16$ . At least 54 institutions, each including 44 participants, need to be included in this study, which brings the total sample size to 2376 participants.

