### **Secondary objectives**

4. To assess the seroprevalence according to vaccination status among NH residents and staff in Belgium at month 0 and at every follow-up visit in the cohort at month 2, 4, 6, 8 and 10.

The seroprevalence among NH residents and staff in Belgium at month 0, and follow-up in the cohort at month 2 (and if relevant at month 4, 6, 8, and 10), will be reported according to the vaccination status (Number of shots: 0, 1 or 2) and for the subgroups ‘with’ and ‘without’ a history of self-reported SARS-CoV-2 infection, averaged over NHs based on a GEE analysis with exchangeable covariance structure.

5. To assess the risk of getting a SARS-CoV-2 infection since vaccination between:
  - Residents and staff
  - Seropositive and seronegative participants at all timepoints
  - Individuals with or without previous self-reported SARS-CoV-2 infections
  - Adjusted for the updated vaccination degree of NH at all timepoints

For vaccinated participants only, a survival analysis will be performed to investigate the time (in days) to a SARS-CoV-2 infection since vaccination between sero-positive and -negative

participants at all time points. A participant is considered to have an event when the participant had a positive PCR test result (or a positive antigen rapid test, or a positive CT scan, or a positive saliva test in absence of a PCR test). The survival or censoring time (in days) is registered since 14 days after being fully vaccinated (full dose regimen) until first event (or censoring moment). If the proportional hazard assumption holds, a stratified (by NH) Cox proportional hazards regression model will be used to model the hazard of SARS-CoV-2 infection between sero-positive and -negative participants at all time points (modelled by the inclusion of a time-varying seropositivity status), adjusted for type of participant, history of self-reported SARS-COV-2 infections, and a time-varying NH vaccination degree. The analysis will be performed stratified by type of participant or other variables, if the proportional hazard assumption does not hold.

6. To assess the proportion of confirmed COVID-19 deaths and non-COVID-19 related deaths since vaccination and the time until death (within the study timeframe) between sero-positive and -negative participants for NH residents

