**Versie voor deelnemende medewerkers:**

1. Gelieve uw uniek studienummer in te vullen.
2. Neemt u nog deel aan de studie (zal deze vragenlijst vervolledigd worden) ?  
Zo neen, waarom niet?

*Door de onderzoeker in te vullen*

- a. Tussentijdse afwezigheid in de studie (ziekte, vakantie, hospitalisatie ...)
- b. Deelnemer wenst niet meer deel te nemen
- a. Vermoedelijk of bewezen COVID-19 overlijden                      datum van overlijden:
- b. Niet-COVID-19 gerelateerd overlijden                      datum van overlijden:
- c. Medewerker is niet langer werkzaam in het WZC

*Vraag 3 wordt enkel toegevoegd indien voordien neen werd geantwoord.*

3. Bent u gevaccineerd tegen COVID-19?
  - a. Ja, 1 dosis
  - b. Ja, 2 dosissen
  - c. Neen
  - d. Zo ja, welk vaccin kreeg u toegediend
    - i. Het AstraZeneca/Oxford vaccin
    - ii. Het BioNtech-Pfizer vaccin
    - iii. Het Moderna vaccin
    - iv. andere
  - e. Zo ja, datum van vaccinatie (eerste spuit).
4. Bent u in de afgelopen twee maanden getest geweest op het coronavirus (via PCR/ag-sneltest/of radiologisch via CT-scan)? Ja/Nee
5. Zo ja. Bent u in de afgelopen 2 maanden (tussen de vorige testronde en nu) positief getest?  
*Meerdere antwoordmogelijkheden*
  - Ja, via PCR-test (test waarbij men via een neuswisser een staal afneemt en u na labo-analyse het resultaat krijgt)
  - Ja, via antigeen sneltest (test waarbij men via een neuswisser een staal afneemt en men binnen het kwartier het resultaat kan aflezen)
  - Ja radiologisch, via een CT-scan
  - neen
6. Zo ja, datum van 1ste positieve PCR-test of sneltest in de afgelopen 2 maanden (bij benadering)?

7. Indien COVID-19 radiologisch bevestigd werd via een CT-scan , vermeld de datum van deze CT-scan.
8. Hebt u in de afgelopen 2 maand (tussen de vorige testronde en nu) een periode 1 of meerdere van volgende symptomen ervaren, zonder dat hier een duidelijke verklaring voor was? Duid aan wat van toepassing is (meerdere antwoordmogelijkheden).
  - Hoest
  - Kortademigheid
  - Pijn op de borst
  - Smaakverlies
  - Geurverlies
  - Verergering van chronische respiratoire aandoeningen (vb. COPD, astma, chronische hoest,...)
  - Koorts
  - Spierpijn
  - Vermoeidheid
  - Loopneus/verstopte neus
  - Keelpijn
  - Hoofdpijn
  - Verlies van eetlust
  - Diarree
  - Acute verwardheid
  - Plotse val
9. Zo ja, wanneer hebt u, bij benadering, deze symptomen ervaren? Gelieve de dag aan te geven waarop deze symptomen zijn begonnen.

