### **Version pour les résidents participants**

(à remplir par l'examineur; à demander par l'infirmière ou l'infirmière en chef ou le représentant du résident):

12. Veuillez saisir le numéro d'étude unique du participant.

13. Le résident participe-t-il toujours à l'étude (ce questionnaire sera-t-il rempli)? Oui Non

Si non, pourquoi pas?

- a. Décès COVID présumé ou prouvé (date du décès)
- b. Décès non lié au COVID-19 (date du décès)
- c. Le résident ne souhaite plus participer

*La question 14 n'est ajoutée que si la réponse était non auparavant.*

14. • Le participant a-t-il été vacciné contre le COVID-19?

o Si oui, quel vaccin le participant a-t-il reçu

- ☐ Le vaccin AstraZeneca / Oxford
- ☐ Le vaccin BioNtech-Pfizer
- ☐ Le vaccin Moderna

o Si oui, date de vaccination (première seringue).

15. Le participant a-t-il été testé pour le coronavirus (via PCR / test rapide ag / ou radiologiquement via CT scan) au cours des deux derniers mois? Oui Non

16. Si c'est le cas. Le participant a-t-il été testé positif pour le coronavirus au cours des 2 derniers mois (entre le cycle de test précédent et maintenant)?

- Oui, via un test PCR (test dans lequel un échantillon est prélevé via un écouvillon nasal et vous obtenez le résultat après analyse en laboratoire)
- Oui, via un test rapide d'antigène (test dans lequel un échantillon est prélevé via un tampon nasal et le résultat peut être lu en 15 minutes)
- Oui, radiologiquement, via un scanner
- Non

17. Si oui, date du 1er test PCR positif ou test rapide au cours des 2 derniers mois (approximative)?

18. Si le COVID-19 a été confirmé radiologiquement par un scanner, indiquez la date à laquelle cela s'est produit.

19. Le participant a-t-il ressenti un ou plusieurs des symptômes suivants au cours des 2 derniers mois (entre le cycle de test précédent et maintenant), sans aucune explication claire à ce sujet? Indiquez ce qui s'applique (options de réponses multiples).

- Toux
- Essoufflement
- Douleur thoracique
- Perte de goût
- Perte d'odeur
- Aggravation des maladies respiratoires chroniques (ex: BPCO, asthme, toux chronique, ...)
- Fièvre
- fatigue musculaire
- Fatigue
- Nez qui coule / bouché
- Gorge irritée
- Mal de crâne
- Perte d'appétit
- La diarrhée
- Confusion aiguë
- Chute soudaine

20. Si oui, quand le participant a-t-il ressenti ces symptômes? Veuillez indiquer le jour où ces symptômes ont commencé.

21. Le cas échéant, le participant a-t-il été vacciné avec un vaccin contre le COVID-19?  

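### The exit branch of the follow-up forms asks for no test result or date, so infections in the interval in which a participant dies or leaves cannot enter the test-based infection endpoint of objectives 5 and 8

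*Protocol*

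**What the plan says.** **Follow-up forms (Protocol, Appendix 6.3).** Question 2 of the Dutch resident form asks "Neemt de bewoner nog deel aan de studie (zal deze vragenlijst vervolledigd worden", that is, whether the resident still takes part, explained in brackets as whether the questionnaire will be completed. The staff form has the same gate, "Neemt u nog deel aan de studie (zal deze vragenlijst vervolledigd worden", and so do the French forms (resident version: "Le résident participe-t-il toujours à l'étude (ce questionnaire sera-t-il rempli").

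A no leads to a list of reasons. For residents these are "Vermoedelijk of bewezen COVID-overlijden (datum overlijden" (suspected or proven COVID death, with date), non-COVID death with date, or refusal to continue. Staff have the same reasons, plus temporary absence and "Medewerker is niet langer werkzaam in het WZC" (no longer employed in the home), the last without a date. The test questions come afterwards; on the resident form they begin with "Is de deelnemer in de afgelopen twee maanden getest geweest op het coronavirus".

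**Endpoint (Protocol, section 3.2).** Objective 5: "A participant is considered to have an event when the participant had a positive PCR test result", with antigen, CT or saliva results accepted where there is no PCR. Objective 8 uses the same tests, reported at baseline or at a follow-up visit. Death from COVID-19 is not an event in either. Non-COVID death is a competing risk in the COVID-19 death analyses (objectives 6 and 9); the infection analyses do not mention death.

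**Other sources.** Section 2.7.2 lists death and leaving the job among the reasons for missing data. The home-level follow-up form gives counts of positive tests and COVID-19 deaths, not linked to participants.

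**The concern.** Take a resident who tests positive two weeks after a round and dies of COVID-19 before the next. At the next round the researcher answers no at question 2 and enters the cause group and the date of death. The positive test is not asked for, no later form follows, and the home-level count cannot be assigned to an individual. In objectives 5 and 8 this resident has no infection event.

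The loss falls on severe infections, because infection itself can cause the exit. Two contrasts are exposed:

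- **Residents versus staff.** Fatal infections are expected mainly in residents, so the resident hazard is understated relative to staff.
- **Seropositive versus seronegative, and vaccinated versus non-vaccinated.** If fatality is higher in seronegative or non-vaccinated participants, more of their events are lost and the contrast moves toward no difference.

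An analysis plan cannot recover a test date that nobody collected.

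**Working it through.** **1. The plan's own drop-out figures.** Section 2.5 sizes the study "assuming a drop-out rate of 0.2 and 0.4 for staff (changes in staff, sick leave and holidays) and residents (deceased, hospitalized or transferred residents". Per home, 10 seronegative staff × 0.8 = 8 and 12 seronegative residents × 0.6 = 7.2, taken as 7. Then 8 + 7 = 15 and 15 × 69 = 1035, as stated. The figures reproduce and are not in dispute.

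Over the whole cohort the rates imply 0.4 × 1656 = 662 residents and 0.2 × 1380 = 276 staff, together 938 of 3036 (31%). This counts all assumed drop-outs, including temporary absence. It is not a count of lost infections.

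**2. How much follow-up lies in exit intervals.** Assume a constant exit rate over five 60-day intervals.

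- Residents: exit per interval q = 1 − 0.6^(1/5) = 0.097; rate λ = −ln(1 − q) = 0.102; mean time observed per interval q/λ = 0.951; share in exit intervals 1 − (1 − q)/(q/λ) = 1 − 0.903/0.951 = 5.0%.
- Staff: q = 1 − 0.8^(1/5) = 0.044, and by the same steps the share is 2.2%.

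Infections unrelated to the exit are therefore affected only to this small extent. The main issue is infections that cause the exit.

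**3. Fatal infections with no form before death.** Assume the positive test falls uniformly within a 60-day interval and death follows L days later. Death precedes the next form with probability (60 − L)/60.

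- L = 14: 46/60 = 77%
- L = 21: 39/60 = 65%
- Wider range: L = 10 gives 83%, L = 30 gives 50%

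**4. Share of resident infection events lost** = fatality × the probability in step 3. The documents give no fatality, so both ranges are assumptions.

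| Assumed fatality | L = 21 | L = 14 |
|---|---|---|
| 1% | 0.65% | 0.8% |
| 5% | 3.3% | 3.8% |
| 10% | 6.5% | 7.7% |
| 30% | 19.5% | 23% |

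If staff lose no events, the resident/staff hazard ratio is multiplied by one minus these values: about 0.96 to 0.99 at 1 to 5% fatality, and about 0.77 to 0.93 at 10 to 30%.

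**5. Serostatus contrast, true hazard ratio 0.50.** Observed ratio = 0.50 × (1 − f₊m)/(1 − f₋m), where f₊ and f₋ are the fatalities in seropositive and seronegative participants and m is the probability in step 3.

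- f₊ = 5%, f₋ = 20%: 0.575, 0.558 and 0.542 at L = 10, 20 and 30.
- f₊ = 1%, f₋ = 5%, L = 14: 0.50 × 0.9923/0.9617 = 0.516.

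**The case against.** **The stop is inferred.** No skip instruction is printed after the no, although the vaccine-hesitancy block of the same appendix does print an end-of-questionnaire instruction. The researcher fills in the resident form from the nurse or representative, so the later questions could be answered after a death. This stands as a limit on certainty. The bracketed gloss and section 2.7.2 still make a stop the natural reading, and nothing asks for the test data after an exit.

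**A reader might infer that these infections are never recorded, or that all fatal infections disappear.** The documents do not support that. A COVID-19 death is recorded individually with its date and, for residents, has its own analysis. Positive tests reported at earlier rounds are kept. By step 3, 23 to 35% of fatal infections reach a form before death at lags of 14 to 21 days. Temporarily absent staff can return and answer for the period since the previous round.

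**A reader might also take 938 (31%) as the size of the problem.** It is not. The rates cover sick leave, holidays, hospitalisation and transfer, and most leavers have no infection in their last interval.

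**The high fatality range may not apply.** Objective 5 covers vaccinated participants only, from 14 days after the full regimen. The lower range belongs in any fair statement of size, and there the effect is slight.

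**The reach is limited.** Both primary objectives use the rapid antibody test and are untouched. Objective 8 depends on enough non-vaccinated participants. If proportional hazards fails, the analysis may be stratified by participant type, and then no resident/staff ratio is estimated. The handling of death may be set out in an analysis plan not shown here, but such a plan could only work with a death item that merges suspected and proven.

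**Conclusion.** The point holds in a limited form. As worded, the exit branch collects no test result or date. Infections in the last interval of participants who die or leave for good, including most rapidly fatal ones, therefore cannot enter the infection endpoint of objectives 5 and 8. The loss depends on the outcome. It lowers the resident hazard relative to staff, and it attenuates the serostatus and vaccination contrasts if fatality is higher in seronegative or non-vaccinated participants.

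The size cannot be fixed from the documents. With 60-day intervals and 14 to 21 days from test to death, about 0.7 to 4% of resident infection events are lost at 1 to 5% fatality and about 7 to 23% at 10 to 30%. The lag and both fatality ranges are assumptions. A single headline bias, such as a resident/staff ratio multiplied by 0.77 to 0.93, is not supported, because it uses only the upper fatality range and assumes that no staff events are lost.

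The affected objectives are secondary and tertiary. The change is still worth making, because the missing data cannot be recovered later.

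**What to change.** 1. In the exit branch of every follow-up form (Dutch and French, staff and residents), for death or permanent departure, add one item: any positive PCR, antigen, saliva or CT result since the last completed form, and its date. For residents take it from the nurse or the home's record; for staff, where available. The resident form lists no transfer or other departure among its reasons, so it needs such an option for the item to reach those residents.
2. Do not collect this item for participants who withdraw consent, since section 5.7 makes consent the legal basis for processing.
3. Split the merged death option into suspected and proven COVID-19 death. Without this, step 4 cannot be applied.
4. In objectives 5 and 8, state that a proven COVID-19 death with no earlier recorded positive test counts as an infection event at the date of death.

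The cost is a few lines in an online form whose exit branch already records dates of death, and one sentence in section 3.2. The downsides are some proxy-reported or approximate test dates, and incomplete data for staff who have left.

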For vaccinated NH residents only, a survival analysis will be performed to investigate the proportion of deaths within the study follow-up and the time (in days) to a confirmed COVID-19 death since 14 days after being fully vaccinated (full dose regimen). The survival or censoring time (in days) is registered since 14 days after being fully vaccinated until first event (or censoring moment). A non-COVID-19 related death will be considered as a competing risk in the analysis. If the proportional hazard assumption holds, a stratified (by NH) Cox proportional hazards regression model will be used to model the cause-specific hazards between seropositive and seronegative residents. The latter will be included as a time-varying covariate. A history of self-reported SARS-COV-2 infections, a time-varying NH vaccination degree, province, age, gender, care profile, and presence of COVID-specific comorbidities will be

considered for model adjustment.

7. To assess the duration of SARS-CoV-2 specific antibody response (seroreversion/no antibody response) since 14 days after being fully vaccinated among NH residents and staff in Belgium.

The duration of SARS-CoV-2 specific antibody responses among NH residents and staff in Belgium will be modelled by means of an interval-censored survival analysis. Seroreversion will be defined as a negative rapid test result after at least one positive rapid test result or as two succeeding negative test results (implying the participant did not seroconvert after vaccination within two to four months). The time interval to seroreversion/no response is the time interval between 14 days after the (second) vaccination date (full dose regimen) and the first test moment of a negative test result after at least one positive rapid test or of the two succeeding negative rapid test results. As a sensitivity analysis, the event will also be defined as two succeeding negative rapid test results (whether or not after at least one positive rapid test result), if the rapid test result would turn out to be unstable.

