### **Tertiary objectives**

Although this study was not designed to assess vaccine effectiveness, end points will be compared between vaccinated and non-vaccinated participants, applying propensity score methods, if sufficient non-vaccinated participants occur in the random selected sample.

8. To assess the risk of getting SARS-CoV-2 infected between vaccinated and non-vaccinated (at last visit) residents/staff.

If a sufficient number of non-vaccinated participants are available in the sample, a survival analysis will be performed to investigate the time (in days) to a SARS-CoV-2 infection

since 14 days after being fully vaccinated between vaccinated and non-vaccinated participants. A participant is considered to have an event when the participant had a reported positive PCR test result (or a positive antigen rapid test, or a positive CT scan, or a positive saliva test in absence of a PCR test) during the baseline or one of the follow-up visits. The survival or censoring time (in days) is registered since 14 days after being fully vaccinated (or since 14 days after main (second) vaccination date in corresponding NH in case of non-vaccinated participants) until first event (or censoring moment).

If the proportional hazard assumption holds, a stratified (by NH) Cox proportional hazards regression model will be used to model the hazard of SARS-CoV-2 infection between staff and residents, and between vaccinated and non-vaccinated participants, adjusting for history of self-reported SARS-COV-2 infections, and a time-varying NH vaccination degree. Propensity score methods will be applied to reduce the effects of confounding. If insufficient non-vaccinated residents would be available in the cohort, the analysis will be performed for staff only.

9. To assess the proportion of confirmed COVID-19 deaths and non-COVID-19 related deaths and the time until death (within the study timeframe) between vaccinated and non-vaccinated residents.

If sufficient non-vaccinated residents would be available, a survival analysis will be performed to investigate the time (in days) to a confirmed COVID-19 death since 14 days after vaccination (or since 14 days after main (second) vaccination date in corresponding NH in case of non-vaccinated participants). A non-COVID-19 related death will be considered as a competing risk in the analysis.

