2.4. Welk vaccin?

2.4.2. AstraZeneca/Oxford vaccin

2.4.3. Het BioNtech-Pfizer vaccin

2.4.4. Het Moderna vaccin

2.4.5. Andere

3. Hoeveel bewoners werden gevaccineerd (in verhouding tot het totale aantal bewoners?)

4. Hoeveel medewerkers werden gevaccineerd (in verhouding tot het totale aantal medewerkers?)

5. Hebt u bewoners/medewerkers georganiseerd laten testen op COVID-19 in de afgelopen 2 maanden (tussen vorige testronde en nu)?

6. Zo ja,

- Via PCR-testing, hoeveel?
- Via antigen sneltesten, hoeveel?

7. Zo ja, wie heeft u laten testen? Duid aan wat van toepassing is.

- Bewoners/medewerkers met symptomen
- Een afdeling/gang (preventief vb. na risicocontact)
- Alle bewoners/medewerkers
- Alleen medewerkers
- Alleen bewoners
- Andere combinaties?: *(open tekstveld)*

8. Zo ja, hoeveel bewoners/medewerkers testten positief?

Voor de PCR test:

Voor de sneltest:

9. Hoeveel bewoners zijn de afgelopen 2 maanden overleden aan COVID-19?

- Aantal bevestigde COVID-19 overlijdens
- Aantal vermoedelijke COVID-19 overlijdens

Individuele vragenlijst

(in te vullen 2-maandelijks in de week dat de test afgenomen wordt)

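### Objectives 6 and 9 analyse confirmed COVID-19 death, but the individual resident forms record suspected and proven COVID death as one option

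*Protocol*

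**What the plan says.** Section 3.2 of the protocol numbers its objectives continuously. The two that matter here are objective 6 (secondary objective 3 in section 2.1) and objective 9 (tertiary objective 2 in section 2.1).

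- **Objective 6**, residents compared by serostatus: "To assess the proportion of confirmed COVID-19 deaths and non-COVID-19 related deaths since vaccination". The analysis concerns "the time (in days) to a confirmed COVID-19 death since 14 days after being fully vaccinated (full dose regimen". It adds: "A non-COVID-19 related death will be considered as a competing risk in the analysis".
- **Objective 9**, vaccinated against non-vaccinated residents: the analysis is to "investigate the time (in days) to a confirmed COVID-19 death since 14 days after vaccination", with the same competing risk. It is run only if enough non-vaccinated residents are available.
- **Individual follow-up form for residents** (appendix 6.3): under the reasons for no longer taking part, the Dutch version has "Vermoedelijk of bewezen COVID-overlijden (datum overlijden" and the French version "Décès COVID présumé ou prouvé (date du décès". Both mean a suspected or proven COVID death. The other two options are non-COVID-19 death, with its date, and withdrawal.
- **Nursing-home follow-up form** (appendix 6.3): "Aantal bevestigde COVID-19 overlijdens" (number of confirmed COVID-19 deaths) has its own line, next to a line for presumed deaths. Both are counts for the home over the past two months.
- **Section 2.7.2**: the Sciensano extract lists homes with their COVID-19 death rate. It places CT and symptoms under suspected, and PCR and antigen test under confirmed.

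**The concern.** A cause-specific hazard analysis needs one cause code and one date for each death. The date is collected. The cause code is coarser than the endpoint: it tells COVID from non-COVID, but not confirmed from suspected. An analyst working from the individual form must either count every death in the combined option as confirmed, which departs from the stated endpoint, or sort the deaths by a rule that the protocol does not give.

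The comparison could also be affected. The (head) nurse or the resident's representative supplies the answers on the resident form, and under section 2.7.3 the head of the nursing staff receives a copy of the resident's antibody result. The person who helps label an uncertain death may thus know the exposure that objective 6 compares. If labelling depended on that knowledge, the cause-specific hazard ratios would be distorted.

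**Working it through.** No sample size, power or event count bears on this point, so the check sets the endpoint beside each source of death data.

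1. **What the analysis needs.** For each resident: a date of death, and a cause that separates confirmed COVID-19 death from non-COVID-19 death, with a defined place for any third category.

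2. **Individual resident forms, Dutch and French.** These record the date of death and two causes: suspected or proven COVID, and non-COVID-19. Confirmed and suspected are not separated. The staff forms merge them too, but staff are outside objectives 6 and 9.

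3. **Nursing-home forms, baseline and follow-up.** Confirmed and suspected deaths are separated, but as counts for all residents of the home, while 24 residents per home are sampled. No participant code is attached. These counts settle an individual death only where every COVID death in that home and period is of one type.

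4. **Sciensano extract.** It separates the categories, but as rates per home.

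5. **Section 2.7.2, individual data.** Death appears as a reason for drop-out, without a confirmed or suspected attribute.

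6. **Test items on the resident follow-up form.** These could show a positive test before death. They come after the question whether the resident still takes part and whether the form will be completed, and death is a reason for answering no. Tests between the last visit and death are therefore not shown to be captured.

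7. **A borrowed definition.** The infection event in objectives 5 and 8 accepts a CT scan when there is no PCR test. In the Sciensano extract of section 2.7.2, CT belongs to suspected death. Using the infection definition to decide which deaths are confirmed would contradict that classification.

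8. **Suspected deaths in the model.** The event is confirmed COVID-19 death and the competing risk is non-COVID-19 death. A suspected COVID-19 death is neither, and it is not said to be censored.

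No source gives an individual confirmed or suspected status, and no adjudication, record linkage or derivation rule is stated.

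For the effect on the estimates, let s1 and s0 be the shares of combined-option deaths that are only suspected in the two groups, and let all of them be analysed as confirmed. In group j the analysed rate is the confirmed rate divided by (1 − sj). The analysed rate ratio is then the confirmed-death ratio × (1 − s0)/(1 − s1). If s1 = s0 the absolute rates rise but the ratio is unchanged; it moves only if the shares differ. The documents give neither share.

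**The case against.** The strongest reply is that the information can be recovered. The researcher completes the resident form by asking a nurse or representative, so there is someone to ask, and the home's own counts settle some cases. This stands against any claim that the endpoint is lost. It does not answer the narrower point: the protocol provides for no such query and states no derivation route.

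A second reply is that the handling of suspected deaths belongs in the SAP, which is not shown. That is fair for the analysis rule. It does not cover data collection, because a SAP cannot separate two categories recorded under one option.

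Three stronger readings are tempting, and the documents do not support them:

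- **That confirmation cannot be rebuilt because the form stops at death.** This is an inference from the wording of the participation question. No stop instruction is printed there, whereas the vaccine-hesitancy block does print one.
- **That hospitalised residents cannot be coded, so informative censoring is hidden.** The resident form has no such option, and section 2.5 names "residents (deceased, hospitalized or transferred residents" as the sources of resident drop-out. But section 2.5 only justifies a drop-out assumption, and section 2.7.3 requires the reason for any test not performed to be documented, with hospitalisation as an example.
- **That the hazard ratios are biased, or the death rate inflated by a known factor.** The first needs shares that differ between the groups, which is plausible but not shown. The second needs a share that the documents do not give.

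**Conclusion.** The mismatch between form and endpoint is real. As designed, the individual death item cannot yield the event for objectives 6 and 9, and suspected COVID-19 deaths have no stated place in the competing-risk analysis. The home-level figures show that the protocol itself regards the two categories as distinct.

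Its size cannot be stated, since it depends on how many deaths in the combined option are only suspected and on whether that share differs between the groups. Its reach is limited to one secondary objective and one tertiary objective that is itself conditional. Seroprevalence, sero-incidence and the sample size do not use cause of death. The point should be fixed, but it does not threaten the main results. The conclusion assumes that the forms in appendix 6.3 are those in use and that no individual cause-of-death source exists beyond those described.

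**What to change.** - On the Dutch and French resident follow-up forms, split the combined option into confirmed COVID-19 death and suspected COVID-19 death, each with the date of death. Record the basis (PCR, antigen test, CT) in a separate field.
- Define confirmed death as in the Sciensano classification of section 2.7.2 (PCR or antigen test confirmed; CT and symptoms suspected), or reconcile that classification with the infection event in objectives 5 and 8, which accepts CT.
- At the next round, query the home or the nurse about deaths already recorded under the combined option.
- In objectives 6 and 9, treat suspected COVID-19 death as a separate cause, with a sensitivity analysis that counts it as COVID-19 death.
- Alternatively, keep the form and redefine the endpoint in sections 2.1 and 3.2 as confirmed or suspected COVID-19 death. This is simpler but gives up the stricter endpoint.

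The cost of the split is one extra tick-box and one basis field per form, and a short query for past deaths.
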